### Intervention

2.3

The exercise intervention will be carried out in the city of Famalicão, 3 days/week, 60 min/day, on pavilions and at municipal gyms whereas the assessment procedures will take place at Faculty of Sport at the University of Porto, since the institution has specific facilities and equipment for this purpose. The intervention length is 12-weeks followed by one washout period of 12-weeks. The expected total study duration is ~8 months, including the baseline and the close-out procedures (Figure 1). The exercise sessions will take place in the morning, on alternating days of the week and will be supervised by experienced exercise physiologists. The sessions consist of a warm-up (5 min), a main part (50 min) and a cooldown (5 min). The warm-up and cooldown will be identical in all three groups, with only the main part being different between the groups.

**Figure 1 fig1:**
[figure not shown]
Descriptive scheme of the study flow and assessments.

Exercise intensity during the sessions will be measured using heart rate (HR) monitors and using the Borg Perceived Exertion Scale (30) across the different groups. The exercise interventions followed the *Consensus on Exercise Reporting Template* (CERT) guidelines (31). All instructors will undergo thorough training to standardize protocols prior to study beginning. All adverse events that occur during the exercise sessions will be recorded. When participants miss two consecutive sessions, they will be contacted by their instructor for support and evaluation. Motivational text messages will be sent to all participants to encourage their continued involvement. Although no other home exercise intervention will be provided to the experimental groups, daily home PA will be assessed in all groups using the FitBit^®^ Zip (San Francisco, CA, United States), and sedentary time, light, moderate and vigorous PA, and step count will be recorded—these data will serve as a covariate in the analysis of the primary outcome. Participants will be discontinued from the exercise intervention if significant adverse events occur [i.e., major cardiovascular (CV) events, hospitalization, major musculoskeletal injury, death or other life-threating situation] or if they engage in another structured exercise intervention (Figure 2).

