#### Randomization

2.2.3

Participants (total *N* = 69) will be randomized into three different groups. After the baseline assessment and eligibility confirmation, the participants study identification sheet will be sent to an independent study team member responsible for the randomization. This study member will generate a list of random numbers using Researcher Randomizer.^1^ This list will define entry order into the randomization process and will allow proper allocation sequence concealment and prevent selection bias. Eligible participants will be randomized to: (*i*) moderate aerobic exercise training [AER: 60–70% HRmax; n = 23]; (*ii*) resistance exercise [RES: 8 exercises/major muscle groups; 8–15 reps; 60–70% 1RM; *n* = 23]; and, (*iii*) a combination of both [RES + AER; *n* = 23] groups at baseline. The randomization will be with a 1:1:1 allocation ratio since all groups are active interventions. The selection of this study design with all “active” groups reduces the possibility of potentially inferior treatment/no treatment and increases volunteers’ acceptability to recruitment. After the randomization, the study team will inform the exercise interventionist about the ID allocation. Due to exercise specificities blinding of participants and exercise instructors is not feasible. However, group allocation will only be communicated to participants immediately before the intervention. The exercise instructors will not perform outcome assessments nor data analysis, and the outcome assessors will be blinded to allocation groups. Participants will be informed to not reveal randomization groups during assessment visits.

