### Assessments

2.5

Participants will be evaluated in three different moments: (i) baseline; (ii) end of the intervention (12 weeks); (iii) close-out (24 weeks). The study has a total duration of 26 weeks. In each study visit, participants will perform the same physical and functional assessments, body composition analysis, and provide a fasting blood and feces sample. Other confounding variables will also be recorded, including nutritional intake (through a 3-day diary), daily PA levels (through a PA tracker), medication intake. Medication and supplementation along with other associated comorbidities will be assessed using a medical questionnaire and medication history questionnaire. Considering the study design, the following outcomes will also be evaluated: (a) retention and attrition rates; (b) adherence to exercise intervention; (c) safety; (d) intervention effect on dependent outcomes (Table 4).

**Table 4 tab4:** Overview of the assessment visits and data collection at each visit.

Study phase	Pre-randomization		Intervention		Follow-up
Visit description	Screening	Baseline	Start	End	CO
Visit number	1	2	3	4	5
Week number	−2	0	2	14	26
Informed consent, review inclusion/exclusion criteria	x				
Demographic information, medical history, medication use	x				
IPAQ questionnaire	x				
Office blood pressure	x	x	x	x	x
Anthropometry measurements	x	x		x	x
Randomization	x				
Body composition (DEXA)		x		x	x
Blood and fecal samples for study assays		x		x	x
Nutritional Intake		x		x	x
Skeletal muscle strength		x		x	x
Physical performance testing		x		x	x
Daily physical activity		x	x	x	x
Assess adverse events			x	x	x
Exercise intervention			x	x	

CO, close-out.

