#### Nutritional intake

2.5.4

All participants will be instructed to record their total food and drink intake during the three consecutive days prior to the day of fecal collection using a food diary. At each of the three scheduled assessment visits (baseline, end of the intervention and close-out), all participants will receive a small brochure, with pre-printed forms, in which they will record the information about the time, type and amount of food and beverages consumed. Together with the delivery of the diary, participants will receive instructions with an explanation and practical examples on how they should record this information. After the 3 days of recording, participants will return the diary booklet (together with the fecal collection sample). The first A5 size booklet, will be delivered in the subsequent experimental periods to help standardize the nutritional intake. This will aid in the analysis of other parameters, since differences in fiber, protein and total energy intake between groups may significantly interfere with the interpretation of the primary and secondary outcomes. After all nutritional data has been collected, food intake will be encoded, and a comprehensive nutrient analysis will be performed with the Food Processor Plus software (ESHA Research).

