### Statistical analysis

2.6

Descriptive and exploratory analyses will be performed, and normality will be assessed using the Kolmogorov–Smirnov or Shapiro–Wilk tests, and if necessary, the data will be transformed for normalization. The differences between the baseline groups will be explored using one-way analysis of variance (ANOVA) or Kruskal-Wallis tests for continuous data and chi-square tests for categorical data.

The intention-to-treat principle will be used for the primary outcome analysis. The main analyses will employ random coefficient linear mixed models for normally distributed endpoints or generalized mixed models for non-normally distributed endpoints. Post-hoc analysis with Bonferroni correction will assess differences between treatment factors. Cohen’s d will be used to indicate the effect size, and significance will be set at *p* < 0.05.

Fecal samples will undergo taxonomic analysis, grouped into amplicon sequence variants (ASVs), and summarized at different taxonomic levels. These data will be imported in R for use with the Phyloseq package. Several indices of alpha and beta diversity will be evaluated (i.e., Simpson Index, Shannon-Wiener Index, Bray–Curtis dissimilarity, Unweighted and weighted Uni-Frac for beta-diversity). Principal Coordinate Analysis (PCoA) will be performed to visualize the dissimilarity matrix between all samples and a PERMANOVA on exercise groups will be performed. Analysis of Compositions of Microbiomes (ANCOM) with bias correction will be used to test for differential abundance of individual ASVs at several levels to compare the three exercise groups. We will use the Benjamin– Hochberg corrected significance level of 0.05 to minimize false discovery rate (FDR). For the metabolomics analysis, samples will be normalized by the total ion current and means centered using Pareto scaling. Univariate analysis of variance will be performed on data from both ion modes to identify variations in peak areas between groups at baseline and after the 12-weeks intervention. Partial least squares discriminant analysis (PLS-DA) will be used to detect the most critical discriminant metabolites in each comparison across groups consistent with published guidelines for metabolomics trials (36). Microsoft packages (e.g., Excell), SPSS (version 27) and R (version 4.2.) software will be used to manage and analyze the different data.

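### The primary analysis adjusts for tracker-measured home activity without limiting it to baseline, so it can depart from the intention-to-treat comparison

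*Protocol article*

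**What the plan says.** All references are to the protocol article.

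- **Section 2.3, paragraph after Figure 1.** The text first notes that no home exercise is prescribed. It then states that "daily home PA will be assessed in all groups using the FitBit" device, lists the tracker quantities, and adds that "these data will serve as a covariate in the analysis of the primary outcome". No time point is given.
- **Section 2.5, Table 4.** The row "Daily physical activity" is marked at baseline (week 0), start (week 2), end (week 14) and close-out (week 26).
- **Section 2.5, text.** Activity is classed as a confounder: "Other confounding variables will also be recorded, including nutritional intake (through a 3-day diary), daily PA levels (through a PA tracker), medication intake".
- **Section 2.6.** "The intention-to-treat principle will be used for the primary outcome analysis". The model is described as follows: "The main analyses will employ random coefficient linear mixed models for normally distributed endpoints", with generalised mixed models otherwise. No covariate or covariate time point is named. The primary null hypotheses at the end of 2.6 compare the randomised groups overall, RES + AER with AER, and RES + AER with RES.
- **Section 2.2.3.** The trial is open to participants: "blinding of participants and exercise instructors is not feasible". Randomisation follows the baseline assessment, and participants learn their group immediately before the intervention.

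**The concern.** Randomisation balances, in expectation, everything that precedes it. A variable measured afterwards has no such protection. Calling in-trial activity a confounder does not make it one for the arm comparison. If the arm changes it, it lies on a path from assignment to outcome. If it also shares unmeasured causes with the outcome (general health, for example), conditioning on it can create an association between arm and outcome that assignment did not produce.

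The model then answers a different question: how the arms would compare among people with equal home activity during the trial. That is not the total effect of being assigned to a regimen, which is what intention to treat and the stated hypotheses concern. The shift can also differ between RES + AER versus AER and RES + AER versus RES, the two contrasts on which the trial's hypothesis rests. Section 2.4.1 says that the data will be used to refine the sample size of a full-scale trial, so a distorted estimate would carry forward.

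**Working it through.** **1. Which readings follow randomisation.** Section 2.2.3 places randomisation after the baseline assessment, so weeks 2, 14 and 26 follow it: three of the four scheduled readings. Table 4, as extracted, marks randomisation at the screening visit (week -2). On either timing these three readings come after it.

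**2. The plan's own figure.** Inputs from 2.2.2: d = 0.9, 80% power, two-sided 0.05, 21 per group. A two-sample t-test needs n = 20.39 per group, rounded up to 21, and power at 21 is 81.2%. The stated 21 is reproduced. It refers to an effect of 0.9 SD with no distortion from a covariate.

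**3. Formula for the shift.** With one covariate M, the adjusted contrast is

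adjusted = (difference in outcome means) - β × (difference in M means).

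Here β is the within-arm slope of outcome on M. If the true effect of assignment is τ and the arms differ in M by a (in within-arm SD), the expected value is τ - a × β, so the bias is -a × β. If a = 0, the bias is zero.

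**4. Inputs.** τ = 0.9 is the plan's target. The documents give neither a nor β. Assumed: a from -0.5 to 0.8 and β of 0.3 or 0.5, both in SD units.

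**5. Results.** Estimates follow from 0.9 - a × β, for example 0.9 - 0.8 × 0.5 = 0.50 and 0.9 + 0.5 × 0.5 = 1.15. Simulation (21 per arm, 20,000 replicates, two-arm analysis of covariance) gave the same estimates to within 0.01, and gave the rejection rates below. In each cell the first value is for β = 0.3 and the second for β = 0.5.

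| a | Estimate when truth is 0.9 | Rejection rate when truth is 0.9 | Type I error when truth is 0 |
|---|---|---|---|
| -0.5 | 1.05; 1.15 | 91%; 98% | 8%; 14% |
| 0 | 0.90; 0.90 | 84%; 90% | 5%; 5% |
| 0.3 | 0.81; 0.75 | 75%; 76% | 6%; 8% |
| 0.5 | 0.75; 0.65 | 66%; 62% | 8%; 14% |
| 0.8 | 0.66; 0.50 | 52%; 39% | 12%; 27% |

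The unadjusted analysis stayed at 0.90, with about 81% power and about 5% type I error throughout.

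**6. Does activity have to cause the outcome?** No. The simulation was repeated with no causal effect of activity and an unmeasured common cause loading 0.55 on both variables, so that the within-arm slope is 0.55 × 0.55 ≈ 0.30. The estimates were again 0.81, 0.75 and 0.66 at a = 0.3, 0.5 and 0.8.

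**7. After the change.** A pre-randomisation covariate has a = 0 in expectation. The a = 0 row applies: no bias, type I error about 5%, and power of about 83.5% to 90% if the baseline value has the assumed slope.

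**Limits.** The check uses one covariate, two arms and one post-treatment measurement. The planned mixed model has three visits and possibly several tracker variables. The check shows the mechanism and does not predict the trial's result.

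**The case against.** The strongest reply is that the sentence in 2.3 gives no time point, a week-0 reading exists, and covariate details are commonly settled in an analysis plan that is not shown. The authors may mean baseline only. That is possible, but it is not the natural reading. The sentence sits in the intervention section, beside the remark that no home exercise is prescribed, and 2.5 describes activity as a confounder recorded across the visits. The sentence also commits these data to the primary analysis, which is more than leaving a detail open.

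A second reply is that home activity may hardly differ by arm. All three arms are active, with the same frequency, session length, warm-up and cooldown (2.3). This stands as a limit on size: the documents show no arm difference, and without one there is no bias. It does not justify a primary analysis that is valid only if that turns out to be so.

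A reader might infer more than the text supports, in three ways:

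- **Session steps.** One might suppose that treadmill work directly inflates the covariate in AER. Section 2.3 targets home activity, and nothing says whether the device is worn in sessions.
- **Diet.** Section 2.5.4 warns that "differences in fiber, protein and total energy intake between groups may significantly interfere with the interpretation of the primary and secondary outcomes". That is a caution about interpretation. It does not put diet in the primary model.
- **Non-wear.** One might suppose that participants without tracker data drop out of the analysis. The article states no rule for missing covariates, so this cannot be claimed.

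**Conclusion.** The point holds as a defect in a stated rule for the primary analysis. As written, the covariate is not limited to baseline, and the natural reading includes values that follow randomisation in an open-label trial. Such an adjustment conflicts with the intention-to-treat comparison in 2.6 and can bias the contrasts in either direction.

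The size is not known. Under the assumed ranges, a true 0.9 SD effect would be estimated anywhere from about 1.15 to 0.50 SD. That is a shift of +0.25 to -0.40 SD, or +28% to -44% of the target (0.25/0.9 and 0.40/0.9). Zero lies within the range. A reader might conclude that the plan is certain to bias the result, or to understate the effect. The documents support neither, because both depend on an arm difference in home activity that they do not report.

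**What to change.** In 2.3, replace the covariate clause with a statement that only the week-0 tracker value, recorded before randomisation, may enter the primary model. In 2.6, state that the primary model is limited to pre-randomisation covariates: baseline *F. prausnitzii* abundance and, if wanted, the week-0 tracker value. Report in-trial activity descriptively by arm, or in a separately labelled exploratory or mediation analysis. Check that the randomisation mark in Table 4 agrees with 2.2.3, so that week 0 is clearly before allocation.

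The cost is about one sentence in each section. All values are already scheduled for collection and the sample size is unchanged. The small downside is that the primary analysis will no longer account for chance differences in home activity during the trial, which the exploratory analysis can show.

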**Figure 2 fig2:**
[figure not shown]
Consolidated Standards of Reporting Trials (CONSORT) diagram—overview of participants flow throughout the study.

#### Resistance exercise protocol

2.3.1

For the RES group, the main part includes free weights, weight machines, and calisthenics; loads will be adjusted based on one repetition maximum (1RM) method. The exercises were standardized, however, when the participants presented limitations, these will be adapted according to participants cardiorespiratory fitness and functional abilities. The protocol for the RES intervention comprises an adaptation period of 3 weeks, followed by 9 weeks of the training-phase as recommended (2). Detailed characteristics of RES protocol regarding the muscle groups, intensity and loads are described in Table 1. The intensity in the RES group is going to be monitored by an HR monitor and by the Borg Perceived Exertion CR10 scale trying to attain an intensity between 5 and 7, which corresponds to a moderate exercise intensity.

**Table 1 tab1:** Exercise training plan and progression- RESISTANCE (RES) Group.

**Week**	**Session**	**Anatomic Region**		**N. Exercises**	**N. Sets**	**N. Reps**	**Load percentage (1RM)**
1	1	Upper limbs	Back	10	1	15	40
	2	Torso	Upper limbs				
	3	Core	Back				
2	4	Core	Torso	8	2	15–20	50
	5	Upper limbs	Back				
	6	Upper Limbs	Upper limbs				
3	7	Torso	Upper limbs	7	2	20	60
	8	Back	Core				
	9	Core	Torso				
4	10	Upper limbs	Upper Limbs	8	3	15	60
	11	Upper Limbs	Back				
	12	Torso	Upper limbs				
5	13	Back	Core	8	3	15	60
	14	Core	Torso				
	15	Upper limbs	Upper limbs				
6	16	Upper limbs	Back	8	3	10	70
	17	Torso	Upper limbs				
	18	Back	Core				
7	19	Core	Torso	8	3	10	70
	20	Upper limbs	Upper limbs				
	21	Upper limbs	Back				
8	22	Torso	Upper limbs	8	3	12	70
	23	Back	Core				
	24	Core	Torso				
9	25	Upper limbs	Upper limbs	8	3	12	70
	26	Upper limbs	Back				
	27	Torso	Upper limbs				
10	28	Back	Core	8	3–4	10–12	70
	29	Core	Torso				
	30	Upper limbs	Upper limbs				
11	31	Upper limbs	Back	8	3–4	12	70
	32	Torso	Upper limbs				
	33	Back	Core				
12	34	Core	Torso	8	3–4	12	70
	35	Upper limbs	Upper limbs				
	36	Upper limbs	Upper limbs				

#### Aerobic exercise protocol

2.3.2

The AER exercise intervention will include walking/jogging in the treadmills, stationary and elliptical bikes in the main part of the sessions. Throughout the sessions, intensity will be measured by maximum HR (HRmax) and by the Rate of Perceived Exertion Scale (RPE 3–5) on category ratio (CR) 10 of Borg’s scale (30) progressing to RPE 6–7. The protocol for the AER intervention was divided into three period that are fully described in Table 2.

**Table 2 tab2:** Exercise training plan and progression-AEROBIC (AER) Group.

Week	Session	Device	N. Sets	Duration (min)	Rest between sets (min)	Load percentage (HRmax)
1	1	Treadmill	3	15	3	50
	2	Stationary bike				
	3	Elliptical bike				
2	4	Stationary bike	3	15	3	50
	5	Treadmill				
	6	Elliptical bike				
3	7	Elliptical bike	2	23	5	60
	8	Stationary bike				
	9	Treadmill				
4	10	Treadmil	2	23	5	60
	11	Treadmil				
	12	Treadmil				
5	13	Treadmill	–	Continuous	-	60
	14	Stationary bike				
	15	Elliptical bike				
6	16	Stationary bike	–	Continuous	–	70
	17	Treadmill				
	18	Elliptical bike				
7	19	Elliptical bike	–	Continuous	–	70
	20	Stationary bike				
	21	Treadmill				
8	22 23	Stationary bike Stationary bike	–	Continuous	–	70
	24	Stationary bike				
9	25	Treadmill	–	Continuous	-	70
	26	Stationary bike				
	27	Elliptical bike				
10	28	Stationary bike	–	Continuous	–	70
	29	Treadmill				
	30	Elliptical bike				
11	31	Elliptical bike	-	Continuous	-	70
	32	Stationary bike				
	33	Treadmill				
12	34	Elliptical bike	-	Continuous	-	70
	35	Elliptical bike				
	36	Elliptical bike				

#### Concurrent exercise protocol

2.3.3

In exercise sessions of the RES + AER group, the main part combined both exercise protocols. The main part will begin with RT using weights, weight machines, and calisthenics combined with moderate AER on the treadmill, stationary and elliptical bikes. The RT part was divided into two phases: an adaptation period of 3 weeks, followed by 9 weeks of a training-phase; in turn, the moderate AT part included 3 phases. Similarly to the previous two protocols, the RES + AER group intensity will be evaluated by the HRmax and by the Rate of Perceived Exertion Scale progressing to RPE 6–7. Table 3 summarize the main characteristics of the exercise intervention.

**Table 3 tab3:** Exercise training plans and progressions-RESISTANCE + AEROBIC (RES + AER) Group.

Week	Session	Anatomic region		N. Exercises	N. Sets	N. Reps	Load percentage (1RM)
1	1	Upper limbs	Back	6	1	15	40
	2	Torso	Upper limbs				
	3	Core	Back				
2	4	Core	Torso	5	2	15–20	50
	5	Upper limbs	Back				
	6	Upper limbs	Upper limbs				
3	7	Torso	Upper limbs	4	2	20	60
	8	Back	Core				
	9	Core	Torso				
4	10	Upper limbs	Upper limbs	4	2	15	60
	11	Upper limbs	Back				
	12	Torso	Upper limbs				
5	13	Back	Core	4	2	15	60
	14	Core	Torso				
	15	Upper limbs	Upper limbs				
6	16	Upper limbs	Back	4	3	6–8	70
	17	Torso	Upper limbs				
	18	Back	Core				
7	19	Core	Torso	4	3	8	70
	20	Upper limbs	Upper limbs				
	21	Upper limbs	Back				
8	22	Torso	Upper limbs	4	3	10	70
	23 24	Back Core	Core Torso				
9	25	Upper limbs	Upper limbs	4	3	12	70
	26	Upper limbs	Back				
	27	Torso	Upper limbs				
10	28	Back	Core	4	3–4	12	70
	29	Core	Torso				
	30	Upper limbs	Upper limbs				
11	31	Upper limbs	Back	4	3–4	12	70
	32	Torso	Upper limbs				
	33	Back	Core				
12	34	Core	Torso	4	3–4	12	70
	35	Upper limbs	Upper limbs				
	36	Upper limbs	Upper limbs				

### Outcome measures

2.4

#### Primary aim

2.4.1

The primary outcome is to assess the change in the relative abundance of *Faecalibacterium prausnitzii* and other SCFA-producing bacteria after the intervention (12 weeks). The change in the relative abundance of *Faecalibacterium prausnitzii* was selected as the primary aim given that, to date, there are no studies of exercise effect on GM nor a consensual marker of microbiome health status in these patients (32), and thus, the preliminary data collected in this study, will help us to refine our sample size and study procedures for a full-scale RCT. In addition, it has been shown that patients with sarcopenia have decreased abundance of this bacterial strain- a known SCFA-producing bacteria, with an important role on systemic inflammation, anabolic resistance, insulin sensitivity, and energy production (5, 15). Secondary outcomes are the change in relative abundance of *Faecalibacterium prausnitzii* at close-out (24 weeks), the change in the relative abundance of the genera Lactobacillus and Bifidobacterium after the intervention and at the end of follow-up.

